#### **4.17 Trial treatment**

Prednisolone and placebo tablets will be manufactured by Essential Nutrition Ltd.

Subjects will be randomised to the active treatment or control arm. Subjects randomised to the active treatment arm will receive a supply of 100 prednisolone tablets for use at the time of development of URTI consistent with study intervention criteria. Subjects randomised to the control arm will receive an identically labelled supply of matching placebo tablets. For subjects unable to swallow the tablets whole, the prednisolone and placebo tablets can be crushed and a tablet crusher will be supplied with the study drug at the prescriber's request.

The pharmacy at Birmingham Women's and Children's NHS Trust will dispense and label the drugs and be responsible for drug accountability in line with their local policy. Study drug (2 containers of 50 tablets of prednisolone or placebo) will be contained within standard containers – these will be sent to the study subject's home or an alternative address via Royal Mail Special Delivery following subject randomisation. Subjects will receive storage information with their study drug. If requested, study drug can be sent to the local investigator who is then responsible for ensuring the subject receives the study drug.

Compliance with study drug will be assessed at each study visit; this will be done by a manual pill count by an appropriate staff member at the local site, using a standard counting triangle.

#### **4.18 Concomitant medications**

All other medications are allowed as required through the trial. These should be recorded in the subject Case Report Forms (CRFs).

#### **4.19 Vaccination**

Where the subject is due for routine vaccination, or specialised vaccinations, there are some contraindications which need to be taken into account as stated in the Department of Health's Immunisation Against Infectious Disease 1996, otherwise known as "The Green Book".

Live vaccines can, in some situations, cause severe or fatal infections in immunosuppressed individuals due to extensive replication of the vaccine strain. For this reason, severely immunosuppressed individuals should not be given live vaccines, and vaccination in immunosuppressed individuals should only be conducted in consultation with an appropriate specialist. Inactivated vaccines cannot replicate and so may be administered to immunosuppressed individuals, although they may elicit a lower response than in immunocompetent individuals.

Subjects who receive prednisolone, orally or rectally, at a daily dose (or its equivalent) of 2mg/kg/day for at least one week, or 1 mg/kg/day for one month are classified as a special risk group for being given live vaccines. Administration of live vaccines should be postponed for at least three months after immunosuppressive treatment has stopped, or three months after levels have been reached that are not associated with immunosuppression. Live vaccines include MMR and the BCG vaccine for tuberculosis. Also for parents who may wish to travel with their children other live vaccines include Yellow Fever and oral typhoid.

Where these issues arise with a subject within the trial please seek the advice of an immunologist or specialist within the field.

#### **4.20 Follow-up assessments**

All subjects will be followed-up for 12 months from randomisation, with subjects reviewed prior to randomisation and then once every three months for trial follow-up assessments (i.e. at 3, 6, 9 and 12 months post randomisation). This is entirely in keeping with the normal frequency of follow-up of this population in routine clinical practice. Follow-up assessments may be made by any appropriately qualified health professional included on the site delegation log. This may include study nurses or clinical nurse specialists as appropriate.

All parents and/or subjects will have previously been trained to perform early morning urine protein estimation as a part of routine clinical practice. They will be provided with a subject-held record book to enter the results of urine protein testing and the medication administered on a daily basis. This will be maintained for the 12 month duration of the study; monitoring of daily urinalysis forms part of routine care for this patient population. Parents will also use this diary to record any intercurrent illness and or consultations with healthcare professionals (GP, nurse, hospital A+E departments etc.), development of URTI and commencement of study medicines, along with details of medicines prescribed or purchased over the counter. Information from diaries reported by parents and subjects to consultants should be recorded in the medical records and on the study CRF. Please copy any patient diaries that are brought into clinic by the parent/participant and keep a copy in the patient notes and the site file. If the patient diaries are not returned to clinic, please record this in the patient notes. If the patient diaries are returned to clinic but are blank, please also record this in the patient notes.

#### **4.21 Study visits**

At the baseline visit:

- Confirmation of inclusion and exclusion criteria.
- Informed consent/assent.
- Randomisation and allocation of study number.

- Information will be captured on dates of last two relapses.
- Medical and drug history since diagnosis of nephrotic syndrome.
- A physical examination will be performed, including measurement of height, weight and blood pressure.
- Calculation of dose of study drug to be administered when URTI occurs and provision of written information for parents regarding this.
- Scoring of prednisolone adverse effects will be performed by use of a standardised proforma.
- In order to evaluate changes in subject behaviour associated with the different prednisolone regimens, the Achenbach Child Behaviour Checklist (ACBC) will be used. The ACBC is a standardised measure made up of 120 items measuring internalising (withdrawn, somatic complaints, anxiety/depression, thought problems) and externalising (social problems, attention problems, delinquent and aggressive) behaviour problems. A total Behavioural Problem score is calculated from these problem scales and forms the basis of comparison with age and gender-matched normative data.
- Information relating to quality of life will also be collected using the CHU-9D and EQ-5D (dependent upon subject age) and PedsQL questionnaires.

At subsequent study visits (months 3, 6, 9 and 12):

- Details will be collected about any URTI that has developed and whether study drug has been commenced.
- Information will be captured regarding recent history of relapse and any treatment received for this.
- Recent other medical/drug history will be recorded.
- Adverse events will be documented.
- A study drug compliance check will be performed (tablet count using counting triangle).
- A physical examination will be performed, including measurement of height, weight and blood pressure.
- Scoring of prednisolone adverse effects will be performed by use of a standardised proforma.
- Recalculation of dose of study drug to be administered when URTI occurs and provision of written information for parents regarding this.
- If 3 or more courses of study drug have been administered since previous visit, confirmation of parental understanding of definition of URTI.
- Information will be collected about consultations with health care professionals in primary care (including the home) and also in hospital (both outpatient and inpatient) and any treatment administered.
- A record will be made of all medicines taken, including those prescribed and those purchased over the counter.
- Repeat administration of the Achenbach, CHU-9D and EQ-5D (dependent upon subject age) and PedsQL will be performed.
- A blood sample for DNA and RNA analysis will be collected at one single visit.
- At the final (12 month) study visit, any remaining study drug will be returned to the Birmingham Children's Hospital Pharmacy for accountability.

## 4.22 Data Collection

The CRF will comprise of the following forms:

| Form                             | Summary of data recorded                                                                                                                                      | Schedule for submission                                                                                                     |
|----------------------------------|---------------------------------------------------------------------------------------------------------------------------------------------------------------|-----------------------------------------------------------------------------------------------------------------------------|
| Randomisation Notepad            | Subject details, confirmation of eligibility and clinical details.                                                                                            | Details collected via online randomisation and copy sent to BCTU following randomisation.                                   |
| Baseline and follow-up CRFs      | Clinical details, primary care visits, hospital admissions, hospital A&E visits, hospital outpatient visits, study drug, adverse effects, subject withdrawal. | Details collected via online data entry system at each follow-up assessment time point (baseline and months 3, 6, 9 and 12) |
| Serious Adverse Event (SAE) Form | Details of any SAE occurring over the 12 month study period and up to 3 months post treatment                                                                 | Faxed/emailed within 24 hours of research staff becoming aware of event.                                                    |
| CHU -9D                          | Child Quality of Life (parent rated)                                                                                                                          | Details collected via online data entry system after follow-up assessment at month 0, 3, 6, 9 and 12.                       |
| EQ-5D                            | Child Quality of Life (parent rated)                                                                                                                          | Details collected via online data entry system after follow-up assessment at month 0, 3, 6, 9 and 12.                       |
| PedsQL                           | Child Quality of Life (parent rated)                                                                                                                          | Details collected via online data entry system after follow-up assessment at month 0, 3, 6, 9 and 12.                       |
| Achenbach (ACBC)                 | Child behaviour (parent rated)                                                                                                                                | Sent to BCTU after follow-up assessment month 0, 3, 6, 9 and 12.                                                            |

Data from all CRF documents, except for the Achenbach Child Behaviour Checklist and SAE form, should be entered online directly by site staff at <http://www.bctu.bham.ac.uk/PREDNOS2>. To access the online data entry system, authorised staff at sites will be provided with an individual secure login username and be requested to set-up a password. Completed copies of the Achenbach Child Behaviour Checklist and SAE form should be forwarded to the PREDNOS 2 Trial Office for data entry. For details regarding the return of completed SAE forms, please see section 5.4 of the protocol.

Data reported on each eCRF should be consistent with the source data or the discrepancies should be explained. If information is not known, this must be clearly indicated on the eCRF. All missing and ambiguous data will be queried. All sections are to be completed before returning.

Any information received from any source (parent/patient contact, patient diaries etc.) regarding development of URTIs and related symptoms, relapse dates and treatment, commencement of study medication, commencement or change of any medication (especially prednisolone and other immunosuppressive therapies), must be documented in the patient notes.

All missing and ambiguous data will be queried via Data Clarification Forms (DCFs). Responses should be made via amendments to the eCRF. The original DCF should be kept in the site file, and a copy of the completed DCF should be returned to the PREDNOS 2 Trial Office.

In all cases it remains the responsibility of the Investigator to ensure that the eCRF has been completed correctly and that the data are accurate.

Trial forms may be amended by the Study Office, as appropriate, throughout the duration of the trial. Whilst this will not constitute a protocol amendment, new versions of the form must be implemented by participating sites immediately on receipt.

## **4.23 Outcome Measures**

### **4.23.1 Primary study endpoint:**

First URTI-related relapse of nephrotic syndrome during 12 month follow-up period.

Relapse is defined as Albustix positive proteinuria (+++ or greater) for 3 consecutive days or the presence of generalised oedema plus 3+ proteinuria. URTI-related relapse is defined as a relapse occurring within 14 days of the development of an URTI.

### **4.23.2 Secondary endpoints/outcome measures:**

Rate of URTI-related relapse of nephrotic syndrome (relapses per year)

Rate of relapse (URTIs-related and non URTIs-related) of nephrotic syndrome (relapses per year)

Cumulative dose of prednisolone (mg/kg and mg/m^2) received over the 12 month study period

Incidence of SAEs

Incidence of adverse effects of prednisolone including assessment of behaviour using the Achenbach Child Behaviour Checklist

Incidence of escalation of background immunosuppressive therapy (e.g. addition of ciclosporin, tacrolimus, cyclophosphamide etc.)

Incidence of reduction of background immunosuppressive therapy (i.e. cessation of long term maintenance prednisolone therapy)

Quality of life using the CHU-9D, EQ-5D and PedsQL

Cost per relapse of nephrotic syndrome

Cost per QALY gained

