|----------------------------|----------------------------------------------------------------------------------------------------------------------------------------------------------------------------------------------------------------------------------------------------------------------------------------------------------------------------------------------------------------------------------------------------------------------------------------------------------------------------------------------------------------------------------------------------------------------------------------------------------------------------------------------------------------------------------------------------------------------------------------------------------------------------------------------------------------------------------------------------------------------------------------------------------------------------------|
| Objectives                 | 
prednisolone given at the time of URTI
 
i] Reduces the overall rate of URTI-related relapse of nephrotic syndrome (expressed as relapses per year).
 
ii] Reduces the overall rate of relapse of nephrotic syndrome (expressed as relapses per year).
 
iii] Reduces the cumulative dose of prednisolone received over the 12 month study period.
 
iv] Reduces the incidence and prevalence of adverse effects of prednisolone including behavioural abnormalities.
 
v] Reduces the number of subjects undergoing escalation of background immunosuppressive therapy (e.g. addition of ciclosporin, tacrolimus, cyclophosphamide etc.).
 
vi] Increases the number of subjects undergoing reduction of background immunosuppressive therapy (e.g. cessation of ciclosporin or long term maintenance prednisolone therapy).
 
vii] Is more cost effective than standard therapy.
     |

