| 4.4. Secondary outcome measures                                                                                                                                                                                                                                                                                                                                                                                                                                                                                                                                                                                                                                                                               |
| 
The secondary outcomes are as follows:
 
 
i. Rate of URTI-related relapse of nephrotic syndrome
 
ii. Rate of relapse (URTJ-related and non URTI-related) of nephrotic syndrome
 
iii. Cumulative dose of prednisolone (mg/kg and mg/m^2) received over the 12 month period
 
iv. Incidence of serious adverse events (SAEs)
 
v. Incidence of adverse effects of prednisolone including assessment of behaviour using the Achenbach Child Behaviour Checklist
 
vi. Incidence of escalation of background immunosuppressive therapy
 
vii. Incidence of reduction of background immunosuppressive therapy
 
 |

- viii. Quality of life using the PedsQL (0=worst, 100=best). See Section 9.4 for questionnaire scoring.
- ix. Cost per relapse of nephrotic syndrome
- x. Cost per QALY gained

The secondary outcomes measures ix and x relate to the health economic analysis and are not part of this SAP.

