#### **Incidence of Escalation/Reduction of Background Immunosuppressant Therapy:**

The background treatment regimen is collected at each of the follow up time points. Data on second line immunosuppressants is also collected (ciclosporin, tacrolimus, levamisole, mycophenolate mofetil, mycophenolate sodium, azathioprine, cyclophosphamide and rituximab). The background treatment regime is categorised into the following four categories:

1. No long-term alternate day prednisolone or other long-term immunosuppressive therapies
2. On long-term alternate day prednisolone only
3. On both long-term alternate day prednisolone and other long-term immunosuppressive therapies
4. On other long-term immunosuppressive therapies only

The background treatment regimen and second line immunosuppressant information will be used in the following way to calculate escalation/reduction of background immunosuppressant therapy:

*Escalation will be computed based as per the following criteria –*

- If a patient is in category 1 from the background treatment regime at previous visit and then at a following time-point is in category 2, 3 or 4 of the background treatment regime then this is considered as an escalation.
- If a patient is in category 2 from the background treatment regime at previous visit and then at a following time-point is in category 3 or 4 of the background treatment regime then this is also considered as an escalation.
- If a patient is in category 4 from the background treatment regime at previous visit and then at a following time-point is in category 3 of the background treatment regime then this is also considered as an escalation.
- If the participant is not on cyclophosphamide or rituximab at previous visit but are then given cyclophosphamide or rituximab at the following time-point then this is also considered as an escalation.
- If participant has an addition of any immunosuppressant (e.g. addition of ciclosporin) in between follow up visits then this is considered an escalation.
- If the participant has a change in medication from Levamisole to either Tacrolimus, Ciclosporin or Mycophenolate then this is also considered as an escalation.

*Reduction will be computed based as per the following criteria –*

- If a patient is in category 3 from the background treatment regime at previous visit and then at a following time-point is in category 4, 2 or 1 of the background treatment regime then this is considered as a reduction.

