- If a patient is in category 4 from the background treatment regime at previous visit and then at a following time-point is in category 2 or 1 of the background treatment regime then this is also considered as a reduction.
- If a patient is in category 2 from the background treatment regime at previous visit and then at a following time-point is in category 1 of the background treatment regime then this is also considered as a reduction.
- If participant on an immunosuppressant (except cyclophosphamide or rituximab) at one time point, but is no longer on it at the following time point then this is also considered as a reduction.

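### The protocol outcome defines reduction as stopping maintenance prednisolone, but SAP 9.4 tests a broader event; the two disagree on 4 of 12 regimen changes, and some drug swaps count as both escalation and reduction.

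*Combined protocol and SAP*

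**What the plan says.** The protocol words this outcome in two ways. The outcome lists in the synopsis and in section 4.23.2 both give "Incidence of reduction of background immunosuppressive therapy (i.e. cessation of long term maintenance prednisolone therapy", which reads as a definition. Secondary objective vi in the synopsis speaks of "reduction of background immunosuppressive therapy (e.g. cessation of ciclosporin or long term maintenance prednisolone therapy", which reads as a list of examples and includes a non-steroid agent. Item v of the synopsis secondary analyses refers to reduction of immunosuppressive therapy with no restriction to prednisolone.

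SAP section 4.4 lists the outcome simply as "Incidence of reduction of background immunosuppressive therapy". SAP section 9.4 then derives it from four regimen categories:

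- 1: neither maintenance prednisolone nor another agent
- 2: "On long-term alternate day prednisolone only"
- 3: both
- 4: other agents only

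The reduction list includes a child "in category 4 from the background treatment regime at previous visit and then at a following time-point is in category 2 or 1", and also this single-agent rule: "If participant on an immunosuppressant (except cyclophosphamide or rituximab) at one time point, but is no longer on it at the following time point". The escalation list includes a child "in category 2 from the background treatment regime at previous visit and then at a following time-point is in category 3 or 4", and also a change from levamisole to tacrolimus, ciclosporin or mycophenolate.

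Under SAP 9.6, the number of children with a reduction is analysed in the same way as the primary outcome, so it yields an adjusted risk difference, a relative risk and a p-value.

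**The concern.** A reader of outcome vii in the protocol expects to learn how many children came off maintenance steroids. The SAP analysis answers a different question: how many children had any qualifying step down in immunosuppression, including steps that leave prednisolone in place and one that starts it. Because the result is formally tested, the choice of definition fixes a reported effect estimate.

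A second problem lies inside the SAP. Its lists are not mutually exclusive, and no rule says what happens when one change meets both. Replacing levamisole with tacrolimus is an escalation by an explicit rule, and it also satisfies the single-agent reduction rule because levamisole has stopped. One treatment step-up would then also count as a favourable event.

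**Working it through.** The plan states no figure for this outcome that could be reproduced, so the check is a full enumeration. Each SAP category is coded by whether the child takes maintenance prednisolone and whether the child takes another agent. Four categories give 4 × 3 = 12 possible moves. Each is scored under protocol outcome vii (event if prednisolone goes from yes to no) and under the SAP 9.4 category rules.

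| Move | Prednisolone | Other agent | Protocol outcome vii | SAP category rules |
|---|---|---|---|---|
| 1→2 | started | none | no | escalation |
| 1→3 | started | started | no | escalation |
| 1→4 | none | started | no | escalation |
| 2→1 | stopped | none | reduction | reduction |
| 2→3 | kept | started | no | escalation |
| **2→4** | stopped | started | **reduction** | **escalation** |
| 3→1 | stopped | stopped | reduction | reduction |
| **3→2** | kept | stopped | **no** | **reduction** |
| 3→4 | stopped | kept | reduction | reduction |
| **4→1** | none | stopped | **no** | **reduction** |
| **4→2** | started | stopped | **no** | **reduction** |
| 4→3 | started | kept | no | escalation |

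The two agree on eight moves (three are reductions under both, five under neither) and disagree on four.

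**Effect of the protocol's broader wording.** If objective vi governs, stopping another agent is also a reduction, so 3→2, 4→1 and, read literally, 4→2 become protocol events. Move 2→4 still contains a prednisolone stop that the SAP category rules do not count as a reduction.

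**Single-agent rule.** It adds SAP-only events within a category, for example dropping one of two second-line agents. It also creates the double count for levamisole switches. Whether it covers prednisolone is not stated: the second-line list in SAP 9.4 omits prednisolone, while protocol section 3.3 describes prednisolone as an immunosuppressant. If it does cover prednisolone, 2→4 scores as both escalation and reduction. The disagreements at 3→2, 4→1 and 4→2 stay under either reading.

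**Illustration of dilution (rates assumed).** Protocol section 4.2 expects a roughly even split over the four regimens, so take 25% in each. Assume that 20% of children in each of strata 2, 3 and 4 have a reduction, and that half of the stratum 3 reductions are of the non-steroid agent.

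- SAP events: 0.75 × 20% = 15%.
- Protocol events: 0.25 × 20% + 0.25 × 20% × 0.5 = 7.5%.
- True relative risk of 1.50 on prednisolone cessation and 1.00 on other agents: (7.5 × 1.5 + 7.5)/15 = 1.25.
- Stratum 3 share of one quarter: protocol events 8.75%, giving (8.75 × 1.5 + 6.25)/15 = 1.29.
- Stratum 3 share of three quarters: protocol events 6.25%, giving (6.25 × 1.5 + 8.75)/15 = 1.21.
- Equal effect on other agents, share of one half: (7.5 × 1.5 + 7.5 × 1.5)/15 = 1.50, so no dilution.

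The illustration uses baseline strata, whereas the SAP compares successive visits, and it gives the swaps 4→2 and 2→4 no weight of their own.

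**The case against.** The strongest reply is that the SAP carries out the protocol's stated objective, whose examples are given as "e.g. cessation of ciclosporin or long term maintenance prednisolone therapy". On that view the outcome list is merely worded too narrowly, and changing it would settle 3→2 and 4→1 without touching the analysis. This stands in part: the protocol contradicts itself, and nothing in it shows that the narrow wording is the intended one. It does not remove the need to reconcile, because both places that list the outcome use the narrow wording.

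A reader might infer that the SAP generally scores prednisolone starts as reductions and stops as escalations. It does not. There is one move of each kind, 4→2 and 2→4, and both are swaps. The starts at 1→2, 1→3 and 4→3 are escalations, and the stops at 2→1, 3→1 and 3→4 are reductions. The category rules are in fact consistent with a ranking of 1, 2, 4, 3 from least to most treatment, although the SAP never states one. Move 2→4 is also an escalation under protocol section 4.10, which treats the addition of a new agent as intensification. So listing it as an escalation is not the fault; failing to count the prednisolone stop may be.

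A reader might also infer an unrecorded change of outcome, because the SAP amendment table has no entry for it. That table records changes from SAP version 1.0, which is not available here. If the same rules stood in that version, no entry was due.

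Finally, cumulative prednisolone dose is a separate secondary outcome, the SAP rules are the same for both arms, and they were set before final database lock. All of this limits the consequence.

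**Conclusion.** The point holds as a mismatch of definitions. The event named in protocol outcome vii is not the event that the SAP tests. They differ on 4 of 12 category moves, or on 3 for certain if the single-agent rule is read to include prednisolone. No passage explains the difference. Separately, the SAP lets an agent-to-agent switch count in both directions.

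The size in children is unknown, because the documents give no frequencies for these moves. It is tempting to say that a true relative risk of 1.5 would be reported as about 1.2 to 1.3. That needs an assumed event rate, an assumed mix of agents and, above all, no effect on other agents. With an equal effect on those agents there is no dilution, so the documents do not support that figure as an expected bias. This is a secondary outcome; the primary analysis and the sample size are not affected.

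**What to change.** 1. Bring synopsis objective vi, outcome vii in the synopsis and in protocol 4.23.2, and SAP 4.4 and 9.4 to one definition.
2. In SAP 9.4 and 9.6, report two separately labelled components in the modified ITT population: cessation of long-term maintenance prednisolone, and cessation of another immunosuppressant. Do not limit the first to children on prednisolone at randomisation. The protocol sets no such limit, and it would lose a child who starts and then stops during follow-up.
3. State whether prednisolone counts as an immunosuppressant in the single-agent rule.
4. State how swaps are scored (4→2, 2→4 and agent to agent). A swap that the SAP lists as an escalation should not also count as a reduction merely because the replaced agent stopped. The prednisolone stop at 2→4 should still count under the prednisolone component.

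The cost is SAP and protocol wording and one extra table; regimen category and second-line agents are already collected at follow-up. The drawback is fewer events, and so less precision, for each component than for the pooled event. These changes concern how the outcome is scored and leave treatment rules as they are.
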